### **8.5 Accountability and Disposal**

At the research centre, investigational product will be stored in a locked area with limited access. During the study, the investigational product accountability form, the dispensing log and the log of returned drug will be kept and monitored.

All returned drug will be returned to the investigational product dispenser or pharmacy at the end of each visit. At the end of the study, the unused drug will be destroyed after the approval of the sponsor and according to the research centre's SOP for destruction of investigational product.

**9.0****ASSESSMENTS****9.1 Safety and Tolerability Assessments****9.1.1 Clinical adverse events**

Occurrence of clinical adverse events (including Serious Adverse Events) will be collected following an open question to volunteers on the time points according to the Schedule of Procedures (Appendix A1). The adverse events will be graded using the Appendix B, Adverse Event Grading Toxicity Table as a guideline. For more information regarding adverse events refer to Section 10.0, Adverse Events.

**9.1.2 Concomitant Medications**

During the study, information regarding concomitant medications and reasons for their use will be solicited from the study volunteers at each visit and recorded. Concomitant receipt of investigational products is prohibited during the study.

**9.1.3 Routine laboratory parameters**

Table 3 shows the laboratory parameters that will be measured routinely. These tests will include haematology and clinical chemistry. The samples for these tests will be collected at the time points indicated in the Schedule of Procedures (Appendix A1).

**Table 3**  
**Laboratory Parameters**

| Laboratory Parameter | Test                                                                                                                                                |
|----------------------|-----------------------------------------------------------------------------------------------------------------------------------------------------|
| Haematology          | Full blood count (haemoglobin, leucocytes, platelets)
Differential count ( absolute neutrophil count, absolute lymphocyte count)                 |
| Clinical Chemistry   | Creatinine, creatinine clearance, serum phosphate,
Liver function tests: aspartate transferase (AST), alanine transferase (ALT), total bilirubin |

**9.1.4 Specific screening tests:**

Volunteers will be screened to exclude or detect the following diseases:

- Pancreatitis: Serum amylase
- Hepatitis B: positive for hepatitis B surface antigen (HbsAg)
- Syphilis: confirmed diagnosis of active syphilis
- Chlamydia: urine nucleic acid probe for chlamydia
- Gonorrhoea: urine nucleic acid probe for gonorrhoea
- In females, vaginal swab for trichomonas, candidiasis and bacterial vaginosis

### **9.1.5 Specific tests in the event of HIV infection**

HIV-uninfected partners who are found to be HIV-infected during the study will be tested for:

- CD4+ T cell count
- HIV viral load
- P24 antigen and other assays for early seroconversion and virus detection
- HIV genotyping for drug resistance mutations
- Viral tropism assays
- HIV sequencing

## **9.2 Immunology Assessments**

### **9.2.1 Antibody Responses**

Serum antibodies against HIV antigens will be measured by ELISA at the time points indicated on the Schedule of Procedures (Appendix A1). Sponges/Swabs will be used to collect mucosal secretions for antibody secretion. SOPs for collection, processing and storage of these specimens will be developed in collaboration with IAVI collaborators and investigators. Immunoglobins such as IgA will be extracted from thawed secretions and assayed by ELISA. If IgA and/or IgG responses are detected in mucosal secretions and/or serum, these specimens may be further evaluated in functional antibody assays such as HIV neutralization assays at suitable testing facilities.

### **9.2.2 Cellular Responses**

Blood for immunogenicity assays will be taken at time points indicated in the Schedule of Procedures. PBMC will be processed, cryopreserved at 10 million PBMC/vial and stored in accordance with established IAVI SOPs as outlined in the Laboratory Analytical Plan. As the immune response in individuals on PrEP has previously not been evaluated systematically, in this protocol some exploratory evaluations of immune responses will be undertaken. As new information from pre-clinical studies and human studies becomes available on what immune responses develop and/or which assays might detect such immune responses during PrEP treatment, this knowledge will be applied to the IAVI studies. Cell mediated immune responses will be evaluated using PBMC and population-based HIV overlapping peptide pools or optimized HIV peptide sets, as described in the Laboratory Analytical Plan. The first tier assay may include ELISPOT (standard and more sensitive cultured assay format) for monitoring the number of circulating T-cells that can be stimulated to produce cytokines such as IFN- $\gamma$  and IL-2. The ELISPOT assay will be conducted at the research centres where feasible. If ELISPOT responses are detected, further characterization of phenotype and functional properties of responding T-cells will be performed using multi-parameter flow cytometry and functional assays, including a viral inhibition assay (VIA), which measures the composite CD8+ T lymphocyte antiviral activity. Proliferative capacity and activation status of circulating and mucosal mononuclear cells will also be evaluated using

flow cytometry techniques. An algorithm may be applied to prioritize assays based on available specimens from each of the FTC/TDF daily, FTC/TDF intermittent, placebo daily, or placebo intermittent treatment groups.

Where possible the immunology studies will be conducted at the research centres. However the multi-parameter flow cytometry requires sophisticated equipment which is currently only available at the Core Lab and the Uganda Virus Research Institute (UVRI). The VIA assay requires containment level three tissue culture facilities. Attempts will be made to transfer assays and reagents to participating laboratories. Further studies may be carried out using a) individual peptides in a matrix or other format to determine the specific epitopes recognized and b) peptides from different HIV-subtypes. Selected T-cell responses may be further characterized for HLA restriction and additional markers on the responding cells, such as markers for activation or homing to mucosal tissues.

### **9.2.3 PBMC, Serum and Plasma Storage**

Further details regarding the type of collection tube, the volume of blood, and specimen handling procedures can be found in the Laboratory Analytical Plan, and in the research centre and laboratory SOPs.

Plasma and serum stored samples will be archived in two locations for potential future testing and quality control, with one portion at the research centre's laboratory and the other portion at a central, quality controlled laboratory. Samples will be catalogued and stored in conditions that ensure appropriate power supply back-up and accurate sample retrieval. PBMCs will be used for assessments of immune functions, HLA mapping, genetic analyses, virus isolation and other HIV and immune system-related tests. Genetic analyses will be limited to those factors that may influence HIV acquisition and disease in population based studies or metabolism of the study drug. PBMCs will be separated at local laboratories using sponsor-approved SOPs and stored at one central laboratory (IAVI Core Laboratory) under Good Clinical Laboratory Practices (GCLP) conditions.

Ethics Review Committee notification or approval will be obtained for all sample requests and testing performed on archived samples that are not described in the list above. Samples may be stored indefinitely at selected outside laboratories under the current Ethics Committee (EC) approval. All specimens will be shipped in accordance with International Air Transport Association specimen shipping regulations for infectious materials.

Stored samples will be shipped routinely from each research centre to the IAVI Core Laboratory or other designated contract laboratories or collaborating institutions.

The immunological testing will be performed at the research centres where feasible and at the IAVI Core Laboratory in accordance with IAVI standard operating procedures and standard reagents.

### 9.3 Acceptability Assessments

Acceptability of the investigational product and study regimen will be assessed through follow-back interview and focus group/individual interview at the time point indicated in Appendix A1. Reported willingness to use the study regimen, if shown to be effective will be the main measure of acceptability.

The acceptability of certain study procedures will also be assessed, including IVR or SMS to record sexual activity data, MEMS TrackCaps and hair sampling to measure adherence.

### 9.4. Adherence Assessments

Adherence to and dosing of investigational product will be assessed through MEMS data, follow-back interview and plasma/intracellular drug levels at the time points indicated in Appendix A1.

*MEMS electronic medication-monitoring pill bottle caps.* Daily medication adherence data will be collected using the AARDEX Medication Event Monitoring System (slightly larger than a standard pharmacy-sized bottle cap with an electronic chip that clocks bottle openings in a 24-hour period). This measure provides complete information on patterns of adherence, including treatment interruptions. Each volunteer will be assigned a MEMS TrackCap to be used on his or her study drug pill bottles. MEMS data for all volunteers regardless of assignment group will be uploaded from the device at monthly visits as indicated in Appendix A1.

*Self-reported adherence.* At timepoints indicated in the Schedule of Procedures (Appendix A1) self-reported adherence to PrEP will be collected using a follow-back interview which is a structured self-report of number of doses missed. A 30 day self-report was shown to be closely associated with MEMS adherence in Uganda [77,110].

*Plasma drug levels.* Plasma from all volunteers will be stored at multiple visits as indicated in Appendix A1 for retrospective assessment of drug plasma levels in those volunteers assigned to FTC/TDF. The plasma half-life of tenofovir after a single oral dose is approximately 17 hours, but drug remains detectable (>10ng/mL) out to 48 hours [43]. At the end of the study after treatment assignment has been unblinded, samples will be selected from up to 4 visits when the volunteer's MEMS data indicate dosing with FTC/TDF within 48 hours of the visit and tested for plasma drug levels.

Two additional adherence measurements will be explored. Intracellular drug levels will be measured in volunteers assigned to FTC/TDF. PBMCs will be collected from all volunteers at the time points indicated in Appendix A1. After

treatment assignments are unblinded, samples from volunteers assigned to FTC/TDF will be tested for intracellular drug levels. The relationship between adherence pattern and intracellular drug level will be explored to see if these drug levels could be used as a proxy for adherence in future studies. Similarly, hair samples will be collected from all volunteers, tested for drug levels in volunteers assigned to FTC/TDF and correlated with adherence patterns. Hair collection will take place at the time points indicated in Appendix A1.

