|                         | 
Acceptability:
 

• The proportion of volunteers who report willingness to use the study regimen

• The acceptability to the HIV-infected partner of their partner using the investigational product

 
Intracellular drug concentrations:
 

• The mean intracellular drug concentration for each group assigned to FTC/TDF

 
Adherence:
 

• The proportion of volunteers who took, by MEMS (Medication event monitoring system) data, at least 80% of expected doses of the investigational product

• The proportion of volunteers assigned to FTC/TDF who have detectable drug plasma levels within 48 hours of reported use.

• The relationship between intracellular drug levels and adherence in volunteers assigned to FTC/TDF

 
Behavioral:
 

• Reported number of steady and casual sex partners

• Frequency of unprotected vaginal intercourse

• Substance use prior to or during sex

 
Other:
 

• The proportion of volunteers who report somewhat high or high levels of burden in using electronic medication monitoring to measure adherence, and using cell phone communication to measure sexual activity

• The proportion of study days with missing sexual activity data

• The proportion of volunteers who report sharing medications

• The proportion of volunteers assigned to placebo who have detectable intracellular drug levels

• The proportion of HIV-infected partners in discordant couples not on ART with detectable drug levels

• The proportion of volunteers with HIV-specific immune responses as measured by analysis of cellular or humoral immune response, or changes in gene regulation as measured by microarray or proteomic techniques

 |                         |                |                         |         |       |    |         |              |    |         |       |    |         |              |    |

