### **4.2 Other Objectives**

To prepare study teams for larger PrEP trials

To evaluate methods for measuring adherence and sexual activity

To evaluate potential for medication sharing

To evaluate HIV-specific immune responses in volunteers randomized to FTC/TDF and to placebo

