**5.1.2 Other Endpoints**

- The proportion of volunteers who report somewhat high or high levels of burden in using electronic medication monitoring to measure adherence, and IVR or SMS to measure sexual activity
- The proportion of study days with missing sexual activity data
- The proportion of volunteers who report sharing study medication.
- The proportion of volunteers assigned to placebo that have detectable intracellular drug levels
- The proportion of volunteers with HIV-specific immune responses as measured by analysis of cellular or humoral immune response, or changes in gene regulation as measured by microarray or proteomic techniques

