## 9.6 Medication Sharing Assessments

Potential for medication sharing will be assessed through the follow-back interview at the time points indicated in Appendix A1.

In discordant couples, it will also be assessed by retrospective intracellular drug levels on HIV-infected partners of volunteers assigned to FTC/TDF. Blood specimens from the HIV-infected partner will be stored at 2 visits. A subset of these samples will be tested retrospectively for drug levels.

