#### **14.2.7 Medication sharing**

Medicine sharing will be assessed by follow-back interview. Medicine sharing between members of discordant couples will also be assessed by drug levels in the HIV-infected partner

Drug levels in hair samples of study volunteers assigned to FTC/TDF groups will be evaluated for exploratory purposes only.

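### The protocol lists drug detection in placebo volunteers as an endpoint, but its assay plan schedules no placebo sample for intracellular testing

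*Protocol*

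**What the plan says.** **Endpoint.** Section 5.1.2 lists "The proportion of volunteers assigned to placebo that have detectable intracellular drug levels". The synopsis carries the same item under Other endpoints: "The proportion of volunteers assigned to placebo who have detectable intracellular drug levels". It serves an objective in section 4.2: "To evaluate potential for medication sharing".

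**Assay plan.** Section 9.4 says "Intracellular drug levels will be measured in volunteers assigned to FTC/TDF". It then has PBMC collected from all volunteers, and says that after "treatment assignments are unblinded, samples from volunteers assigned to FTC/TDF will be tested for intracellular drug levels". Plasma is handled the same way, being stored from all volunteers "for retrospective assessment of drug plasma levels in those volunteers assigned to FTC/TDF". Hair is also collected from everyone and tested in the FTC/TDF groups.

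**Medication sharing.** Section 9.6 relies on the follow-back interview and on stored samples from the HIV-infected partners of FTC/TDF volunteers, and adds: "A subset of these samples will be tested retrospectively for drug levels". Section 14.2.7 opens with "Medicine sharing will be assessed by follow-back interview". It adds drug levels in the HIV-infected partner and exploratory hair levels in the FTC/TDF groups. Neither section mentions an assay in placebo volunteers.

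**The concern.** A listed endpoint needs a data source. Here the section that decides whose samples go to the laboratory names only the active arms, and it does so by contrast with collection, which covers everyone. A laboratory working from section 9.4 would leave the placebo samples in the freezer.

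What would be lost is a direct biological check for active drug reaching placebo volunteers, whether through sharing or a dispensing error. Placebo recipients are the comparator for immune response (14.2.8) and for the adverse-event contrast (14.2.1), so such exposure bears on both. Without the assay, evidence of drug reaching placebo volunteers would rest mainly on the interview. Section 3.3.3.1 warns of social desirability bias in participant reports. That warning concerns reported adherence, but a similar bias in reports of sharing is plausible, because section 7.6 has counsellors discuss reasons not to share pills.

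**Working it through.** **1. Who is sampled and who is assayed**

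| Protocol section | Sampled | Assayed for drug |
|---|---|---|
| 9.4, intracellular | all volunteers | FTC/TDF volunteers, after unblinding |
| 9.4, plasma | all volunteers | FTC/TDF volunteers |
| 9.4, hair | all volunteers | FTC/TDF volunteers |
| 9.6, sharing | HIV-infected partners, 2 visits | subset of samples from partners of FTC/TDF volunteers |
| 9.7.1 | collection only | not stated |
| 14.2.7, sharing | not stated | HIV-infected partners (no arm or subset named); hair in FTC/TDF groups, exploratory |
| Appendix A1, drug-level row | same for all arms | arm not stated |

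No row sends a placebo volunteer's sample for assay. The Appendix A1 row has testing in its title and does not differ by arm, but section 9.4 is the more specific text and narrows it.

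**2. Denominator.** Section 14.1 gives 24 combined placebo recipients (12 daily plus 12 intermittent, section 5.2.2). Samples scheduled for intracellular assay: 0 of 24. The protocol gives no precision or power figure for this endpoint, so there is none to reproduce.

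**3. What the endpoint would deliver if all 24 were assayed.** With no positives, the exact two-sided 95% upper limit is 1 − 0.025^(1/n).

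- n = 24: 1 − 0.025^(1/24) = 0.1425.
- n = 12 (one placebo regimen): 1 − 0.025^(1/12) = 0.2646.
- One positive in 24: exact interval 0.0011 to 0.2112.
- Two positives in 24: exact interval 0.0103 to 0.2700.

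The chance of at least one positive among 24 is 1 − (1 − p)^24, where p is the true proportion detectable at the visit. The values of p are assumed, since the protocol gives none:

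- p = 2%: 38%.
- p = 5%: 71%.
- p = 10%: 92%.

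**4. What one sample can show.** Section 3.1.4 gives intracellular half-lives of 39 hours (FTC triphosphate) and at least 60 hours (tenofovir diphosphate). Taking five half-lives as a rough detection window (an assumption):

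- FTC: 5 × 39 = 195 hours, about 8 days.
- Tenofovir: 5 × 60 = 300 hours, 12.5 days, or longer because 60 hours is a lower bound.

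The dosing period is 16 × 7 = 112 days, so one sample covers roughly 8/112 = 7% to 12.5/112 = 11% of it under that assumption.

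**The case against.** The strongest reply is that section 9.4 concerns adherence, where only active-arm levels are informative. It does not say *only* and does not forbid placebo testing. The endpoint itself implies a placebo measurement, PBMC are held for everyone, and the Appendix A1 row is not arm-specific. On this view the assay description merely omits some samples. It stands to this extent: a reader might infer that placebo testing is prohibited or can no longer be done, and the protocol supports neither. But the sections on medication sharing, where the missing instruction would belong, do not supply it. A laboratory plan or SAP not shown might add the assay, but it would then be at odds with section 9.4.

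Four stronger readings are tempting and are not supported:

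- *The placebo assay is the only objective check.* Undetectable plasma drug in an FTC/TDF volunteer soon after a recorded MEMS event (9.4), allocation-number matching at dispensing (8.3), pill counts (8.4) and partner drug levels (9.6) are also checks, though indirect for this question.
- *Section 14.2.7 confines partner assays to one arm or to a subset.* It does neither. Only the exploratory hair levels are tied to FTC/TDF.
- *The partner endpoint also has no data.* Section 9.6 speaks of a subset of samples stored at two visits, which may mean one visit per partner. Any subset still yields a proportion. Testing every partner without regard to treatment would also overlook the synopsis condition that the partner is not on ART.
- *A clean result would rule out contamination above 14.25%.* Step 4 shows that one sample covers only recent exposure.

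It is also fair to say that this is not a primary endpoint, and that section 14.2.1 already admits limited power for the safety contrast. Both points limit the importance of the gap but do not remove it.

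**Conclusion.** The inconsistency holds. The synopsis and section 5.1.2 promise a proportion among placebo volunteers, while the assay plan in section 9.4 names only FTC/TDF volunteers and nothing in 9.6 or 14.2.7 makes up the difference. As written, 0 of 24 placebo volunteers are scheduled for assay and the endpoint has no data. It can be recovered because the PBMC are collected. It is worth correcting because the remedy is cheap and restores an endpoint serving a stated objective.

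The 14.25% limit assumes that all 24 placebo volunteers supply a usable sample at the chosen visit and that none is positive. It bounds detectable exposure in the days before that visit. The conclusion about the missing assay does not depend on any of these figures.

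**What to change.** In section 9.4 or 9.6, and again in 14.2.7, state that at least one stored post-randomization PBMC sample from every placebo volunteer, taken at a fixed visit (for example Week 16), will be assayed for intracellular drug. Code the placebo and FTC/TDF samples so that the laboratory cannot tell the arm. Reserve the aliquot in advance, because the same PBMC collection also supplies the immune assays, which section 9.2.2 allows to be prioritised by specimen availability. In 14.2.7, report the proportion with its exact 95% interval and describe it as recent detectable exposure at that visit.

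If the sponsor does not want the assay, delete the endpoint from the synopsis and section 5.1.2. That also removes the contradiction but gives up the check.

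Cost: about 24 assays on stored material (24 × 1.1 = 26.4, so some 26 if the permitted 10% over-enrolment is used), with no new visits or blood draws.

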## 9.5. Behavioural Assessments

Behavioural Assessments will be assessed through IVR or SMS and follow-back interview at the time points indicated in Appendix A1.

*Interactive voice response or SMS measurement of daily sexual behavior.* Based on methods of Schroder[140], volunteers will be provided with a SIM card or a cell phone for the daily measurement of sexual behaviour using either IVR or SMS. Participants will be contacted daily to digitally answer questions similar to the following questions: 1) Did you have sex with your main partner yesterday? 2) (if yes) Did you use a condom? 3) Did you have sex with any other partner yesterday? 4) (if yes) Did you use a condom? Data will be recorded via entering the numerical response via cell phone keypad (press 1 for yes, 2 for no). Total interview time will be under 60 seconds. To encourage daily reporting, individuals will be reimbursed with 3 minutes of air time for each call. Individuals not responding will be contacted again by cell phone to elicit a response. Breach in confidentiality via unauthorized use will be prevented through automatic confirmation of the assigned cell phone number and asking the volunteer to enter a password to confirm his/her identity prior to the questions. All volunteers will have an instructive session on the use of the system.

*Follow-back interview.* The timeline follow-back interview is a calendar-aided face-to-face interviewing method during which participants are asked to retrospectively report daily sexual behaviour. This approach has shown strong retest reliability [141, 163]. Interviewers will be trained according to the method developed by Sobell and Sobell [164]. Interviewer gender will be matched to the gender of the volunteer. Volunteers will be given a customized calendar. Volunteers will be asked to mark personal “anchor” days or “holidays” on the calendar such as a market days, church attendance, national holidays, or weddings [164]. Volunteers will mark each day they had intercourse, the number of sexual partners, and code whether a condom was used. Additional risk data will be collected, such as substance use before or during sex.

